# A phase II single arm study of Nivolumab with stereotactic Ablative radiation Therapy after induction chemotherapy in CHOlangiocarcinoma (NATCHO)

**DOI:** 10.1186/s12885-022-10373-1

**Published:** 2022-12-12

**Keywords:** Nivolumab, Immunotherapy, PD-1 inhibitor, Cholangiocarcinoma, Biliary tract cancer, Radiotherapy, Chemotherapy

## Abstract

**Background:**

Intrahepatic cholangiocarcinoma (CCA) is amongst the most common primary liver tumors worldwide. CCA carries a bad prognosis prompting research to establish new treatment modalities other than surgery and the current chemotherapeutic regimens adopted. Hence, this trial explores a new therapeutic approach, to combine stereotactic body radiation therapy (SBRT) and immunotherapy (Nivolumab), and asses its clinical benefit and safety profile after induction chemotherapy in CCA.

**Methodology:**

This is a Phase II open-label, single-arm, multicenter study that investigates Nivolumab (PD-1 inhibitor) treatment at Day 1 followed by SBRT (30 Gy in 3 to 5 fractions) at Day 8, then monthly Nivolumab in 40 patients with non-resectable locally advanced, metastatic or recurrent intrahepatic or extrahepatic CCA. Eligible patients were those above 18 years of age with a pathologically and radiologically confirmed diagnosis of non-resectable locally advanced or metastatic or recurrent intrahepatic or extrahepatic CCA, following 4 cycles of cisplatin-based chemotherapy with an estimated life expectancy of more than 3 months, among other criteria. The primary endpoint is the progression free survival (PFS) rate at 8 months and disease control rate (DCR). The secondary endpoints are overall survival (OS), tumor response rate (TRR), duration of response, evaluation of biomarkers: CD3 + , CD4 + and CD8 + T cell infiltration, as well as any change in the PD-L1 expression through percutaneous core biopsy when compared with the baseline biopsy following 1 cycle of Nivolumab and SBRT.

**Discussion:**

SRBT alone showed promising results in the literature by both inducing the immune system locally and having abscopal effects on distant metastases. Moreover, given the prevalence of PD-L1 in solid tumors, targeting it or its receptor has become the mainstay of novel immunotherapeutic drugs use. A combination of both has never been explored in the scope of CCA and that is the aim of this study.

**Trial registration:**

ClinicalTrials.gov NCT04648319,
April 20, 2018.

**Supplementary Information:**

The online version contains supplementary material available at 10.1186/s12885-022-10373-1.

## Background

Intrahepatic cholangiocarcinoma (CCA), which arises from the bile ducts [1], is amongst the most common types of liver tumors worldwide [2] making up around 3% of gastrointestinal cancers [3]. In the United States, CCA is the second most common primary hepatic malignancy with around 5,000 newly diagnosed cases per year [2]. With a 5-year survival of less than 10%, the prognosis is due to late stage presentation to clinic, high rate of metastasis and recurrence and the restricted amount of treatment modalities [4]. Although surgery persists as the only curative management plan, it is often not an option as only less than 20% of patients are candidates due to advanced stage at diagnosis. The remainder of the patients with advanced and unresectable CCA would undergo chemotherapy which presents with many limits [5–8]. With chemotherapy, the median OS for patients with an unresectable tumor is relatively low, ranging from 7 to 12 months. In addition, in surgical candidates, the recurrence rates reach up to 50%, and the post-resection survival rate at 5 years ranges between 8 to 44% [5, 7, 9–12]. In the absence of any treatment, the OS is 6 months regardless if the tumor is primary or recurrent [5, 9, 11–13].

Current chemotherapy regimens for patients with advanced CCA include gemcitabine, whether alone or in combination with platinum agents, or 5-fluorouracil [14]. Several studies have shown that the use of cisplatin and gemcitabine as a combination chemotherapy regimen has a significant survival advantage and can hence be used as a preferable treatment option for patients with advanced biliary cancer [14, 15]. Nevertheless, single or combination chemotherapy regimens have not been consistent in tumor shrinkage, prevention of recurrence, and increasing survival rate more than 8 to 15 months. As such, it is necessary to study and establish new treatment modalities in these patients. This protocol attempts to establish a new plan of treatment, composed of a potentially effective combination of radiotherapy and immunotherapy, or more specifically Stereotactic body radiation therapy (SBRT) and Nivolumab.

SBRT has been under the spotlight for a good while now. In a phase I trial 41 patients with inoperable cancer were recruited (10 intrahepatic CCAs and 31 hepatocellular carcinomas) to undergo SBRT (36 Gy over 6 fractions). Upon completion, the median OS for all patients was 13.4 months, survival at 1 year was 51%, and local control rates at 1 year were 65% [16]. Within the first 3 months, treatment related adverse events (AE) were restricted to grade 1–3 and no radiation-induced liver disease was noted. These favorable results led to more phase II and phase III trials studying the efficacy of 6 fraction SBRT. In another phase II trial, 46 patients with intrahepatic CCA were administered a high-dose conformal radiation therapy with concurrent hepatic artery floxuridine. Patients had a median OS of 13.3 months, which is improved versus historical control groups [17]. Consequently, SBRT is becoming more reliable as a management plan for patients with unresectable disease, as it seems to have promising clinical benefit and a good safety profile in these patients.

Moving on, the role of immunotherapy is being investigated in advanced biliary tract cancers (BTC). Durvalumab, an anti-PDL-1 agent, showed promising results in a phase I/II trial in comnation with tremelimumab in patients with HCC and BTC, with 42% of the patients in the BTC cohort achieving stable disease. Ongoing trials are evaluating the therapeutic efficacy of durvalumab in BTC as monotherapy or in combination with other checkpoint inhibitors, chemotherapy or local therapies [18]. Nivolumab is a monoclonal antibody that blocks PD-L1 and PD-L2 and their interactions with the PD-1 receptor. A single-group phase II study by Kim et al. (2020) administered nivolumab to 54 patients with BTC and showed that not only did it have a relatively good safety profile, but was also moderately effective and with durable response [19]. Another phase II trial by Klein et al. (2020) administered nivolumab and ipilimumab followed by nivolumab to 39 patients with advanced BTC. The trial concluded that there was significant positive outcomes that highlight the need to further investigate anti-PD1 treatment modalities [20].

It is only until recently that Nivolumab started gaining the spotlight in treating advanced CCA, as more clinical trials are currently emerging, combining nivolumab either with other immunotherapy medications or with chemotherapy or with other modalities [21]. Thus, Nivolumab has yet to be extensively and meaningfully studied in advanced BTC, despite the medication demonstrating clinical benefit in several different tumor types (i.e. melanoma, Hodgkin lymphoma, renal cell carcinoma, urothelial carcinoma, squamous cell cancer of the head and neck, and non-small cell lung cancer) and treatment settings [22–28]. Across the aforementioned tumor types, responses with nivolumab were typically observed early during treatment and appear durable in nature. In addition, studies have found that SBRT can produce a synergistic effect with immunotherapy, whereby it elicits changes in the tumor microenvironment, allowing for a better immune response. Dewan et at. demonstrate this in their study, where they showed that anti-cytotoxic T-lymphocyte associated protein 4 (CTLA4) antibody treated mice had an enhanced tumor response to fractionated radiotherapy (30 Gy in 5 sessions or 24 Gy in 3 sessions) at the primary site and at the site outside of the radiation field (abscopal effect) [29].

The current gold standard of therapy for advanced BTC is gemcitabine plus cisplatin as per the National Comprehensive Cancer Network (NCCN) guidelines (version 2021) [30]. The ABC-02 trial followed the same latter regimen [31]. The current trial population and that of ABC-02 share many similarities, which enables us to consider their population as a historical control group. No previous RCT data are available for the combination of high dose SBRT and Nivolumab in locally advanced CCA and there are no on-going trials regarding this topic. The progression free survival (PFS) is expected to reach 42% at 8 months in comparison to 23% in the ABC-02 study. Accordingly, the current trial efficacy and safety results will be compared to those of ABC-02 trial. In the ABC-02 randomized Phase II study, 86 patients with locally advanced or metastatic BTC were recruited to compare cisplatin plus gemcitabine with gemcitabine alone. The median PFS was 8 months in the cisplatin-gemcitabine group and 5 months in the gemcitabine-only group (*p*-value < 0.001). In addition, the rate of tumor control among patients in the cisplatin-gemcitabine group was significantly increased (81.4% versus 71.8%, *p*-value = 0.049). As such, the addition of cisplatin to gemcitabine was associated with a significant survival advantage without the addition of substantial toxicity [15].

In view of the above data, a Phase II clinical study is highly required to evaluate the PFS and the disease control rate (DCR) in patients with non-resectable locally advanced or metastatic or recurrent intrahepatic or extrahepatic CCA following nivolumab and SBRT. In our protocol, we assume that the addition of the immune checkpoint inhibitor, nivolumab, to SBRT will further improve outcomes including PFS and DCR [15].

## Methodology

### Objectives

This trial aims to assess the efficacy and safety of nivolumab with SBRT after induction chemotherapy in patients with CCA. The primary endpoint is the PFS at 8 months and DCR in patients with non-resectable locally advanced or metastatic or recurrent intrahepatic or extrahepatic CCA following Nivolumab/SBRT treatment.

The secondary endpoints are OS, tumor response rate (TRR), duration of response, evaluation of biomarkers: CD3 + , CD4 + and CD8 + T cell infiltration, changes in PD-L1 expression following 1 cycle of nivolumab and SBRT, AE and quality of life.

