### Statistics

For the efficacy endpoint, a land-mark analysis that might be more appropriate for immunotherapy was used to calculate the sample size. In the ABC2 study, the 12- month PFS, calculated from the start of chemotherapy, was 23% [15]. In this study, this would be equivalent to 8-month PFS as eligible patients will be recruited following 4 cycles of cisplatin-based chemotherapy administered over a period of 4 months. This study conservatively aims to increase the 12-month PFS, as defined by the ABC-02 study, to 42%. The sample size calculation comparing a single proportion to a known proportion (42%) yields a sample of 34 patients taking into consideration Type 1 error of 0.05 and power of 0.8. Adding that drop-out or treatment withholding due to patient decision or unacceptable AE occurrence can take place, an additional 15% will be added to yield a total sample size of 40 patients. PFS will be estimated using Kaplan–Meier methods. Median PFS and the PFS rate at 8 months and corresponding 95% CIs will be presented. PFS will be defined for all patients as the time between the date the patient is enrolled in the study and the date on which imaging reveals disease progression or the patient dies, whatever is earlier, and the last follow-up date, in case neither disease progression nor death has occurred. Patients without progression or death will be censored at the last assessment. PFS will be analyzed for all the patients. Exploratory variables will be analyzed according to their scale of measurement by using mean ± standard deviation or frequency distribution for numeric and categorical variables respectively. Frequency distribution for AEs and SAEs will be presented per cycle and per patient. Similarly, this will be done for the SAE of Grade 3 or above combined.

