### Eligibility criteria

For patient inclusion, all of the following criteria must be met:

Signed and dated informed consent form.Patients aged ≥ 18 years.Pathologically (histologically or cytologically) and radiologically confirmed diagnosis of non-resectable locally advanced or metastatic or recurrent intrahepatic or extrahepatic CCA within 90 days of registration.Patients who have SD or PR following 4 cycles of cisplatin-based chemotherapy.ECOG performance score < 3.An estimated life expectancy of more than 3 months.Have adequate hematologic and biochemical function by meeting the following:Total bilirubin acceptable level ≤ 1.5 × the institutional upper limit of normal (ULN) range;Aspartate aminotransferase (AST) and alanine aminotransferase (ALT) acceptable levels up to 5 × ULN range;Serum urea and serum creatinine acceptable levels up to 1.5 × ULN range;Calculated glomerular filtration rate ≥ 45 mL/min according to the Chronic Kidney Disease Epidemiology Collaboration equation (or local institutional standard method). Negative serum or urine pregnancy test at screening for women of childbearing potential who are sexually active.Highly effective contraception for both males and females of child-bearing potential who are sexually active throughout the study and for at least 5 months and 7 months after the last nivolumab treatment administration, respectively.Candidate for percutaneous biopsy as per tumor location evidenced by CT scan and interventional radiologist.

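### DCR is named co-primary with 8-month PFS, but the sample size, type 1 error and power are set for PFS alone, and the implied ABC-02 reference rate for DCR is not comparable.

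*Protocol article*

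**What the plan says.** The Objectives section names two quantities as primary: "The primary endpoint is the PFS at 8 months and DCR in patients with non-resectable locally advanced". The Abstract does the same: "The primary endpoint is the progression free survival (PFS) rate at 8 months and disease control rate (DCR").

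The Statistics section sizes the trial on one of them. The reference rate is PFS: "In the ABC2 study, the 12- month PFS, calculated from the start of chemotherapy, was 23" per cent, which the protocol treats as equivalent to 8-month PFS from enrolment. The target is also PFS: "This study conservatively aims to increase the 12-month PFS, as defined by the ABC-02 study, to 42" per cent. The calculation "yields a sample of 34 patients taking into consideration Type 1 error of 0.05 and power of 0.8", and 15% is added for drop-out to reach 40. DCR does not appear in that section.

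The Background treats ABC-02 as a historical control and adds: "Accordingly, the current trial efficacy and safety results will be compared to those of ABC-02 trial". It then reports that tumour control in the cisplatin-gemcitabine group of ABC-02 "was significantly increased (81.4% versus 71.8" per cent). For DCR itself it gives only a qualitative expectation of improvement.

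Eligibility requires disease control at entry: "Patients who have SD or PR following 4 cycles of cisplatin-based chemotherapy". The exclusion criteria remove patients who progressed on that chemotherapy.

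**The concern.** A primary endpoint is one on which the trial may be declared positive. Two are named here, and the error rate and power are given for one. A reader of the final report could take a favourable DCR as a primary result protected by the stated 5% error and 80% power, when neither figure was derived for it.

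The planned comparison with ABC-02 adds a second difficulty. It is worded for efficacy results in general, so it takes in DCR. The only DCR-type figure reported from ABC-02 belongs to patients randomised to the chemotherapy itself. In this trial that chemotherapy has already been given, and those whose disease it did not control are not enrolled.

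**Working it through.** **Inputs.** From Statistics: PFS 23% (reference), 42% (target), type 1 error 0.05 with sidedness not stated, power 0.8, drop-out 15%. From Background: ABC-02 tumour control 81.4%. Assumptions of this check, not in the protocol: 81.4% as a DCR null, DCR read at the week-16 CT, and true DCR values of 85%, 90% and 95%.

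**1. Reproducing the plan's figure.** One-sample proportion, normal approximation:

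n = [z(1−α)·√(p0·q0) + z(power)·√(p1·q1)]² / (p1−p0)²

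One-sided 0.05: [1.645·√(0.23·0.77) + 0.842·√(0.42·0.58)]² / 0.19² = (0.692 + 0.415)² / 0.0361 = 33.98, so 34. Drop-out: 34/0.85 = 40. A two-sided 0.05 gives 42.6, so 43. The stated 34 therefore uses the whole one-sided 0.05 on PFS and leaves no share for DCR.

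**2. If either endpoint could give success, each at 0.05.**
- Upper bound: 0.05 + 0.05 = 10%. With independence: 1 − 0.95² = 9.75%.
- Exact one-sided tests at n = 40: PFS needs at least 15/40 (actual size 0.028 at 23%), and DCR needs at least 37/40 (actual size 0.045 at 81.4%).
- If DCR is read at week 16, a patient progression-free at 8 months was also controlled at week 16, so the endpoints are nested. Take X ~ Bin(40, 0.814) for DCR and, given X, Y ~ Bin(X, 0.23/0.814) for PFS. Then P(X ≥ 37 or Y ≥ 15) = 6.9%.
- Most of the drop from 9.75% comes from the conservatism of the exact tests: independence with the same actual sizes gives 1 − (1 − 0.045)(1 − 0.028) = 7.2%, or 7.1% before rounding. Nesting removes little more.

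**3. If both were needed.** The error is then controlled without a split, but joint power cannot exceed the lower of the two powers. DCR power against 81.4% (exact, one-sided 0.05):

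| n | Success rule | True 85% | True 90% | True 95% |
|---|---|---|---|---|
| 40 | ≥ 37/40 | 0.13 | 0.42 | 0.86 |
| 34 | ≥ 32/34 | 0.10 | 0.33 | 0.76 |

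With 40 patients, 80% power on DCR alone needs a true rate of about 94%. Even there, joint power is capped by the power for PFS.

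**4. The two DCR populations side by side.**

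| | ABC-02 figure | This trial |
|---|---|---|
| Denominator | Patients randomised to the chemotherapy | Only patients with SD or PR after 4 cycles |
| Time origin | Start of chemotherapy | About 4 months later, at enrolment |
| Disease control at baseline | Not a condition | Required |

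The protocol shifts the time origin for PFS (12 months to 8 months) and makes no corresponding adjustment for DCR. Removing progressors raises the DCR seen here. A first scheduled CT at week 16, some 8 months after chemotherapy began, lowers it. The documents do not say which effect is larger.

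**The case against.** The strongest reply is that the protocol sets no DCR test at all. Statistics speaks of the efficacy endpoint in the singular and describes estimation: Kaplan–Meier, the 8-month rate and 95% CIs. Success rules and multiplicity are commonly left to an analysis plan, which is not shown. That stands in part. The lack of a written DCR rule or definition in an article is not the fault. The fault is that the article itself names two primary endpoints and itself assigns the error and power to one.

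Three stronger readings are tempting and are not supported:
- A reader might infer that the trial runs at a 10% error. The inflation depends on an either-endpoint rule that nobody wrote, and 10% is only an upper bound.
- A reader might infer that 81.4% is the declared DCR null and that the comparison must flatter the new treatment. The comparison sentence follows the PFS figures, and 81.4% appears later as a reported ABC-02 result. It is the implied benchmark, and the direction of the bias is open.
- A reader might note that 81.4% versus 71.8% in 86 patients does not yield the quoted p of 0.049 (about 0.29 with an assumed 43 per arm). This is a background reporting slip. Neither 86 nor 0.049 enters this trial's design, so it deserves a minor correction elsewhere.

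It is also fair to object that the same entry selection affects the 23% PFS reference, which counts from the start of chemotherapy. That is true, and making PFS the sole primary endpoint does not cure it. It needs separate handling.

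**Conclusion.** The point holds in this form. DCR has primary status without any part of the stated sample size, error or power. The mismatch is within the article and needs no assumption: 34 reproduces with the full one-sided 0.05 on PFS.

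The size of the consequence does rest on assumptions. Under an either-endpoint rule, the error is about 7% with nested endpoints, exact tests and nulls of 23% and 81.4%, and never more than 10%. Under a both-endpoints rule, power is at most 42% if the true DCR is 90% and the null is 81.4% with 40 patients. Separately, a DCR comparison with ABC-02 would set a rate in preselected, already controlled patients against a rate in patients starting chemotherapy, with a bias of unknown net direction. The PFS sample size is not undermined by this point; a primary claim on DCR would be.

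**What to change.** In the Abstract and Objectives, name 8-month PFS as the sole primary endpoint, so that the stated error and power apply to it. List DCR as secondary and descriptive, with an exact 95% CI at the week-16 CT that the treatment schedule already contains. In the Background, limit the planned comparison with ABC-02 so that DCR is not set against its tumour control rate.

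This needs wording changes only, with no added patients or visits. The price is giving up a primary claim on DCR. Keeping that claim would cost more. Splitting the error to one-sided 0.025 each raises PFS to 43 evaluable patients (43/0.85, so 51 with drop-out). Detecting 81.4% against an assumed 90% at one-sided 0.05 with 80% power needs [1.645·√(0.814·0.186) + 0.842·√(0.9·0.1)]² / 0.086² = 107.7, so about 108 evaluable patients, and the reference rate would still not be comparable.

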### Study design

This is a phase II open-label, single-arm, multicenter study investigating Nivolumab treatment at Day 1 followed by SBRT radiation treatment (30 Gy in 3 to 5 fractions) at Day 8, then monthly Nivolumab in patients with non-resectable locally advanced, metastatic or recurrent intrahepatic or extrahepatic CCA. One week following SBRT, PD-L1 and T cell infiltration changes will be assessed through percutaneous core biopsy as compared with the baseline biopsy, or from biopsy of the metastatic site in the case of extrahepatic CCA. In this study, 40 patients with non-resectable locally advanced or metastatic or recurrent intrahepatic or extrahepatic CCA patients will be enrolled in total.

This study has been prospectively registered in the registry of clinical trials of the United States of America (ClinicalTrials.gov Identifier: NCT04648319).

### Investigational medicinal product (IMP)

IMP description: Nivolumab (Opdivo®) for intravenous infusion, available as a solution of 10 mg/mL in single-dose vials. The active pharmaceutical ingredient in Nivolumab drug product is a human IgG4 monoclonal antibody, which binds to PD-1 receptor and blocks its interaction with PD-L1 and PD-L2.

#### Trial duration

There is no maximum duration of the treatment duration. Treatment will continue as patients are not progressing or not having any SAE that requires discontinuation of the treatment. The follow-up period is until death. The total period is 3 to 4 years.

### Statistics

For the efficacy endpoint, a land-mark analysis that might be more appropriate for immunotherapy was used to calculate the sample size. In the ABC2 study, the 12- month PFS, calculated from the start of chemotherapy, was 23% [15]. In this study, this would be equivalent to 8-month PFS as eligible patients will be recruited following 4 cycles of cisplatin-based chemotherapy administered over a period of 4 months. This study conservatively aims to increase the 12-month PFS, as defined by the ABC-02 study, to 42%. The sample size calculation comparing a single proportion to a known proportion (42%) yields a sample of 34 patients taking into consideration Type 1 error of 0.05 and power of 0.8. Adding that drop-out or treatment withholding due to patient decision or unacceptable AE occurrence can take place, an additional 15% will be added to yield a total sample size of 40 patients. PFS will be estimated using Kaplan–Meier methods. Median PFS and the PFS rate at 8 months and corresponding 95% CIs will be presented. PFS will be defined for all patients as the time between the date the patient is enrolled in the study and the date on which imaging reveals disease progression or the patient dies, whatever is earlier, and the last follow-up date, in case neither disease progression nor death has occurred. Patients without progression or death will be censored at the last assessment. PFS will be analyzed for all the patients. Exploratory variables will be analyzed according to their scale of measurement by using mean ± standard deviation or frequency distribution for numeric and categorical variables respectively. Frequency distribution for AEs and SAEs will be presented per cycle and per patient. Similarly, this will be done for the SAE of Grade 3 or above combined.

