### Exclusion criteria

Patients who have progression following 4 cycles of cisplatin-based chemotherapy evidenced by CT scan as per RECIST 1.1.Active brain metastases or leptomeningeal metastases.Prior organ transplantation or allogenic stem-cell transplantation.Known prior severe hypersensitivity to IMP or any component in its formulations, including known severe hypersensitivity reactions to monoclonal antibodies (NCI-CTCAE v4.03 Grade ≥ 3).Active infection requiring systemic therapy within 28 days before the first dose of study treatment (e.g., urinary tract infection).Known history of testing positive for the human immunodeficiency virus or known acquired immunodeficiency syndrome.Evidence of liver cirrhosis.Current use of immunosuppressive medication, except for the following:Intranasal, inhaled, topical steroids, or local steroid injection (e.g., intra-articular injection);Systemic corticosteroids at physiologic doses ≤ 10 mg/day of prednisone or equivalent;Steroids as premedication for hypersensitivity reactions (e.g., CT scan premedication).Active autoimmune diseases that might deteriorate upon receiving an immune-stimulatory agent.Conditions such as vitiligo, psoriasis, diabetes type I, or hypo- or hyper-thyroid diseases not requiring immunosuppressive treatment are eligible.Commonly excluded conditions include: Addison’s disease, thyroiditis/Hashimoto’s thyroiditis, systemic lupus erythematosus, Sjogren’s syndrome, scleroderma, myasthenia gravis, Goodpasture’s syndrome, and Grave’s disease.Hepatic insufficiency manifesting as clinical jaundice, hepatic encephalopathy, and/or variceal bleed within 60 days prior to study entry.Transmural myocardial infarction within 6 months of enrollment; provided that anti-platelets cannot be stopped to perform percutaneous biopsy.Congestive heart failure (≥ New York Heart Association Classification Class II) requiring hospitalization within the last 6 months provided that anti-platelets cannot be stopped to perform percutaneous biopsy.Serious cardiac arrhythmia requiring medical treatment provided that anti-platelets cannot be stopped to perform percutaneous biopsy.Recent cerebral vascular accident/stroke within 6 months of enrollment provided that anti-platelets cannot be stopped to perform percutaneous biopsy.End-stage renal disease requiring dialysis.Other severe acute or chronic medical conditions including immune colitis, inflammatory bowel disease, immune pneumonitis, pulmonary fibrosis, or psychiatric conditions including recent (within the past year) or active suicidal ideation or behavior.Treatment with an investigational agent within 28 days before the first dose of study treatment.Prior treatment with any drug or antibody (anti-PD-1, anti-PD-L1, anti-PD-L2, anti-CD137, or anti-CTLA-4 antibody) targeting T cell co-stimulation or checkpoint pathways.Patients suspected by the physician that he/she will not be compliant to the protocol conduct.Pregnant women are excluded from this study; breastfeeding should be discontinued.Patients participating in another clinical trial.Patients not willing to sign the consent form.Any psychiatric condition that would prohibit the understanding or rendering of informed consent.Legal incapacity or limited legal capacity patients receiving other oncology specific medication not authorized in the protocol.

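### The 23% benchmark counts patients who failed in the first 4 months of chemotherapy, whom this trial cannot enrol; the like-for-like null is S(12)/S(4), about 28% on the article's own figures

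*Protocol article*

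**What the plan says.** The Statistics section gives the historical figure and its time origin: "In the ABC2 study, the 12- month PFS, calculated from the start of chemotherapy, was 23"%. It then moves the clock: "In this study, this would be equivalent to 8-month PFS as eligible patients will be recruited following 4 cycles of cisplatin-based chemotherapy", the chemotherapy being "administered over a period of 4 months". The target is put on the ABC-02 scale: "This study conservatively aims to increase the 12-month PFS, as defined by the ABC-02 study, to 42"%. The calculation "yields a sample of 34 patients taking into consideration Type 1 error of 0.05 and power of 0.8", raised to 40 for drop-out. PFS runs from the date of enrolment.

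Entry depends on the outcome of the induction chemotherapy. The Eligibility criteria list "Patients who have SD or PR following 4 cycles of cisplatin-based chemotherapy", and the Exclusion criteria list "Patients who have progression following 4 cycles of cisplatin-based chemotherapy evidenced by CT scan as per RECIST 1.1".

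The Background sets the two percentages directly against each other: "The progression free survival (PFS) is expected to reach 42% at 8 months in comparison to 23% in the ABC-02 study". It also says that the trial's efficacy and safety results will be compared with those of ABC-02.

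**The concern.** Subtracting 4 months moves the time origin but does not change who is counted. The 23% is a share of everyone who started chemotherapy, including those who progressed or died in months 0 to 4. This trial observes only patients who came through those months without progression. Its 8-month PFS therefore estimates a conditional probability, PFS beyond month 12 given PFS beyond month 4, and the historical counterpart is S(12)/S(4).

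With a single arm, the benchmark does the work of a control group. If it is too low, part of any apparent gain over 23% comes from the entry criteria, and the stated error rate does not describe the chance of a false positive finding.

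**Working it through.** **Inputs from the article.** S(12) = 0.23 from chemotherapy start; induction 4 months; target 0.42; type I error 0.05; power 0.80; n = 34, N = 40 (Statistics). Median PFS 8 months and tumour control 81.4% with cisplatin-gemcitabine in ABC-02 (Background). S(4) is not given and has to be assumed.

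**1. Reproduce the plan's figure.** One-sample proportion, normal approximation, one-sided 5%:

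n = [(1.645·√(0.23·0.77) + 0.842·√(0.42·0.58)) / (0.42 − 0.23)]² = 33.98, so 34; 34/0.85 = 40.

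The two-sided version gives 43. The text calls 42% the known proportion, but taking 42% as the null gives 37.7, so 38. The operative null is therefore 23%, tested one-sided.

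**2. S(4) and the matching null, 0.23/S(4).**

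- Weibull through both quoted PFS figures: shape = ln(1.470/0.693)/ln(1.5) = 1.854, where 1.470 = −ln 0.23 and 0.693 = ln 2. S(4) = exp(−0.693·0.5^1.854) = 0.825. Null = 0.23/0.825 = 27.9%.
- Tumour control rate as a proxy for the share able to enrol: null = 0.23/0.814 = 28.3%.
- Sensitivity, S(4) = 0.90: null = 0.23/0.90 = 25.6%.

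**3. Chance of passing against 23% when PFS after month 4 is unchanged, N = 40.** The exact one-sided 5% rule against 23% is at least 15/40, whose size at 23% is 2.8%. The normal-approximation cut-off is 0.23 + 1.645·√(0.23·0.77/40) = 0.339. An exact two-sided 95% lower limit above 23% needs at least 16/40, with size 1.2% at 23%.

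| S(4) | True rate | ≥15/40, exact | Normal approximation | ≥16/40, exact |
|---|---|---|---|---|
| 0.825 | 27.9% | 12.0% | 19.5% | 6.6% |
| 0.814 | 28.3% | 13.2% | 21.2% | 7.3% |
| 0.90 | 25.6% | 6.4% | 11.2% | 3.2% |

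With 34 evaluable patients (≥13/34, size 3.3% at 23%), the first two rows give 12.5% and 13.6% exact, and 18.1% and 19.6% by the normal approximation.

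**4. Target and power on the conditional scale.** The plan's own exact power, 23% against 42% with ≥15/40, is 77%. Against a null of 27.9% or 28.3%, the exact one-sided 5% rule becomes at least 17/40 (size 3.3% or 3.8%). There are two ways to carry the target across:

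- Same hazard ratio: ln 0.42/ln 0.23 = 0.59. The target is 0.279^0.59 = 47.0% or 0.283^0.59 = 47.4%, with exact power 77% or 78%.
- 42% read literally as a 12-month figure and divided by S(4): 0.42/0.825 = 50.9% or 0.42/0.814 = 51.6%, with exact power 89% or 90%. This assumes a larger effect after month 4: ln 0.509/ln 0.279 is about 0.53.

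These counts treat every patient as followed to 8 months. The plan uses Kaplan-Meier estimates, so they are approximations to the planned analysis.

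**The case against.** **The shift is disclosed.** The Statistics section does state the time origin and the 4-month offset. But disclosing the offset does not remove the early failures from the 23%, and the article contains no other adjustment.

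**No success rule is stated.** This stands. The article plans a PFS rate with a 95% confidence interval, and the threshold here is inferred from the test that reproduces 34. Under the stricter confidence-limit reading, the false-positive rate is about 7%.

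**S(4) is unknown.** This also stands. The direction is arithmetic; the size is not. At S(4) = 0.90 the exact rate is only about 6%.

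**Unchanged PFS after month 4 is not the same as an inert regimen.** The article does not say what ABC-02 patients received after month 4, so the calculation describes a regimen that does no better or worse than that history. The inclusion list also names stable disease and partial response but not complete response, which read literally would pull the matching figure slightly the other way.

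**Stronger readings that the article does not support.** A reader might fit an exponential curve and infer a null well above 28%, with a correspondingly worse error rate. Each such curve contradicts a quoted figure: with a median of 8 months, 12-month PFS is 0.5^1.5 = 35%, not 23%; with 23% at 12 months, the median is 12·0.693/1.470 = 5.7 months, not 8. A reader might also infer that power collapses, by testing a true 42% against the higher null. That moves the null and leaves the target behind, although the Statistics section defines 42% on the ABC-02 12-month scale. On one consistent scale, power does not collapse.

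**Conclusion.** The stated equivalence is wrong as written. Whenever any historical patient failed before month 4, the null that matches this trial's population is above 23%. On the article's figures it is about 28%, resting on one of two assumptions for S(4) that agree with each other: the Weibull curve, or the tumour control rate as a proxy.

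If success is the one-sided 5% test behind n = 34, the chance of passing with PFS after month 4 unchanged is about 12-13% (exact, against a true size of 2.8% at 23%) or 20-21% (normal approximation). It is lower if S(4) is higher or the success rule is stricter. Confidence is high in the direction and moderate in the size. N = 40 remains workable once null and target are on the same scale.

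**What to change.** - In Statistics, replace 23% with S(12)/S(4), both read from the ABC-02 cisplatin-gemcitabine PFS curve, and describe it as 8-month PFS among patients progression-free at 4 months.
- Restate the 42% target on that scale and say which conversion is meant: about 47% at the planned hazard ratio of 0.59, or about 51-52% if 42% is divided by S(4).
- Keep N = 40 and restate the power: about 77-78% exact for the first target, 89-90% for the second, to be recomputed once S(4) has been read off.
- State that the test is one-sided and name the null, since the text now labels 42% as the known proportion.
- Correct the Background sentence that sets 42% at 8 months against 23%.

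This is a change of wording and a rerun of the sample-size statement, with no extra patients. The cost is a less favourable benchmark, about 28% in place of 23%.
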